### 2.3. Procedure and Assessment

A matching number of BD patients with and without comorbid ASD will be recruited. The ASD-BD group will be the experimental arm of the study, with the BD-only group as the clinical comparator. Both groups will be followed up for six months after recruitment while receiving treatment with Extended-Release Lithium Salts for clinical indication. Primary and secondary outcome measures will be acquired before treatment initiation (T0), as well as three (T1) and six (T2) months after reaching stable drug dosage (Steady State—SS). At T0, patients will be screened for eligibility and carefully evaluated by means of the following diagnostic tools: the semi-structured DSM-5-based clinical interview Kiddie Schedule for Affective Disorders and Schizophrenia—Present and Lifetime version (K-SADS-PL); the Wechsler Intelligence Scale for Children—fourth edition (WISC-IV); the Autism Diagnostic Observation Schedule—second edition (ADOS-2); and the Autism Diagnostic Interview—Revised (ADI-R).

At each timepoint (T0, T1, and T2), patients will be thoroughly assessed as for clinical routine. The following rating scales will be filled in by clinicians based on parents’ and caregivers’ reports: the Clinical Global Impression (CGI) scale scores and the Children Global Assessment Scale (CGAS) scores. Patients will be also administered the following clinical interviews: the Children Depression Rating Scale (CDRS); the Young Mania Rating Scale (YMRS); the Columbia—Suicide Severity Rating Scale (C-SSRS); the Deliberate Self-Harm Inventory (DSHI); Reactivity, Intensity, Polarity and Stability questionnaire for Youth (RIPoSt-Y). Caregivers will be administered the following clinical rating scales: the Modified Overt Aggression Scale (MOAS) and the Affective Reactivity Index (ARI).

At each timepoint (T0, T1, and T2), patients will be also assessed for safety and tolerability of Extended-Release Lithium Salts treatment according to following procedures. They will be administered the Lithium Side Effects Rating Scale (LiSERS) to evaluate frequency and severity of side effects. Major adverse events will be monitored and reported to the Italian Medicines Agency according to the clinical routine. They will undergo a full clinical assessment including history update for adverse events, physical and neurological examination, and acquisition of physical and vital parameters (i.e., weight, height, blood pressure, heart frequency), as well as blood sampling and EKG. Blood sampling will be performed the day of each visit in the morning through venipuncture. Blood tests will include lithium plasma levels, complete blood count, glucose, triglycerides, cholesterol, blood urea nitrogen (BUN), creatinine, serum electrolytes, liver enzymes, creatine-phosphokinase (CPK), amylase, fT3, fT4, and thyroid-stimulating hormone (TSH). Routine urinalysis will be also performed. Resting EKG will be performed before the visit and examined by expert cardiologists to provide the following parameters: heart frequency, P wave duration, PR interval duration, QRS interval duration, and QT and corrected QT interval duration.

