## Abstract

**Background**: Lithium is the gold-standard treatment for Bipolar Disorder (BD) in both adults and adolescents, effectively managing mood episodes and reducing suicide risk. While its efficacy in neurotypical youth is well established, its use in adolescents with Autism Spectrum Disorder (ASD) and comorbid BD remains under-researched. Here, we present the protocol for a study aiming to evaluate the efficacy and tolerability of Extended-Release Lithium Salts in treating adolescents with BD and comorbid ASD compared to neurotypical BD patients. **Methods**: This longitudinal prospective naturalistic comparative study will enroll lithium-naïve adolescents aged 12–18 with BD, with or without comorbid ASD, from the Department of Child and Adolescent Psychiatry and Psychopharmacology. Participants will be followed for six months while receiving Extended-Release Lithium Salts treatment. Primary outcomes will include mood instability, suicidality, emotional dysregulation, and aggression, assessed through a range of clinical rating scales and diagnostic tools at baseline, three months, and six months. Secondary outcomes will focus on the safety and tolerability of Extended-Release Lithium Salts, with measures including side effect ratings, physical exams, and laboratory tests. **Results**: We hypothesize that Extended-Release Lithium Salts will demonstrate non-inferiority in treating BD symptoms in adolescents with comorbid ASD compared to those without ASD. **Conclusions**: This study is poised to fill a significant gap in the literature by providing critical data on the use of lithium for adolescents with BD and ASD. Findings will inform clinical practice and future research, potentially guiding more personalized treatment approaches for this complex and vulnerable population.

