### 2.5. Sample Size Calculation

Sample size has been estimated using G*Power software (version 3.1.9.7), considering the clinical rating scales described above as outcome measures of the study. Based on previous literature on BD youths treated with lithium [50], the YMRS score was the best available measure to determine the effect size that would be worth testing and thus was taken as the reference. The calculation was based on a repeated measures test between two independent mean differences of the main outcome, establishing the error level at 0.05, power at 0.95, and effect size at 1.06. Based on this setting, a sample size of 40 subjects (20 patients with ASD-BD and 20 BD-only controls) was obtained. However, since a dropout rate of 20% is expected after 6 months of follow-up based on our previous studies, 5 additional participants per group will be recruited, leading to a total number of 50 subjects as the final sample size (25 patients with ASD-BD and 25 BD-only controls).

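### T1 and T2 are dated from reaching a stable dose, which contradicts the six-month follow-up window and leaves patients who never reach one without a scheduled post-baseline assessment

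*Protocol article*

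**What the plan says.** Section 2.3 (Procedure and Assessment) gives the length of follow-up as: "Both groups will be followed up for six months after recruitment while receiving treatment with Extended-Release Lithium Salts for clinical indication". The next sentence places T0 before lithium is started and the later assessments "three (T1) and six (T2) months after reaching stable drug dosage".

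The Abstract uses a plain clock. It says "Participants will be followed for six months while receiving Extended-Release Lithium Salts treatment", with primary outcomes "assessed through a range of clinical rating scales and diagnostic tools at baseline, three months, and six months", and does not mention a stable dose.

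Section 2.3 ties the efficacy scales to T0, T1 and T2. It does the same for tolerability: at these three timepoints "patients will be also assessed for safety and tolerability of Extended-Release Lithium Salts treatment according to following procedures". Those procedures are the lithium side-effects scale, an adverse-event history update, physical and neurological examination, blood tests, urinalysis and EKG. Major adverse events are also monitored under clinical routine, without a link to the visits.

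Section 2.2 restricts entry to lithium-naïve adolescents. Section 2.5 allows for losses on the basis that "a dropout rate of 20% is expected after 6 months of follow-up".

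**The concern.** There are two linked problems.

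First, the two adjacent sentences in Section 2.3 use different time origins. They agree only if a stable dose is reached at the moment of recruitment, which cannot happen in patients who have not yet taken lithium.

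Second, the visit clock starts at an event that occurs after treatment begins and that some patients may never reach. For them T1 and T2 have no date. If the schedule is followed as written, the efficacy comparison (primary aim) and the tolerability comparison (secondary aim) rest on patients who took lithium long enough to stabilise. The study hypothesis is non-inferiority in ASD-BD, so losing treatment failures selectively from that group would make the hypothesis easier to support. Time elapsed since T0 would also differ between groups if one group takes longer to stabilise, which mixes time with the group effect in any change score.

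This matters at protocol level because visit timing decides which data exist. An analysis plan cannot recover assessments that were never scheduled.

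**Working it through.** **The plan's own figures.** Inputs from Section 2.5: effect size 1.06, error level 0.05, power 0.95, dropout 20%. A two-sample t-test, one-sided, gives 20 per group (power 0.950), so 40 in total as stated. A two-sided test would need 25 per group; the article does not state sidedness. Inflation: 20 / (1 − 0.20) = 25 per group, 50 in total, as stated. The allowance is thus 25 − 20 = 5 losses per group.

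**The two clocks.** Let m be the months from first dose to a stable dose. The documents give no value; 0.5 to 3 is assumed. T1 falls at 3 + m and T2 at 6 + m after the first dose.

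| m (assumed) | T1 | T2 |
|---|---|---|
| 0.5 | 3.5 | 6.5 |
| 1 | 4 | 7 |
| 2 | 5 | 8 |
| 3 | 6 | 9 |

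T2 lies outside six months for any m above 0. If the groups differ in m, their T2 visits differ in elapsed time by the same amount.

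**Who has a scheduled post-baseline assessment.**
- Reaches a stable dose and continues: T1 and T2 are both datable.
- Reaches a stable dose, then stops: both are datable, although Section 2.3 describes follow-up as taking place on lithium.
- Stops before a stable dose, or never reaches one: neither is datable.

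**Effect on the comparison.** Let p be the proportion not stabilised, s the mean improvement (in SD) of those who stabilise, and let the others improve by 0. All values are assumed.
- Difference among stabilised patients: s(ASD) − s(BD).
- Difference among all starters: s(ASD) × [1 − p(ASD)] − s(BD) × [1 − p(BD)].

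With s = 1.0 in both groups and p(BD) = 0.10:

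| p(ASD) | Stabilised | All starters |
|---|---|---|
| 0.20 | 0 | 0.80 − 0.90 = −0.10 |
| 0.30 | 0 | 0.70 − 0.90 = −0.20 |
| 0.40 | 0 | 0.60 − 0.90 = −0.30 |

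In the middle row, 0.30 × 25 = 7.5 ASD-BD and 0.10 × 25 = 2.5 BD-only patients would have no scheduled tolerability assessment after T0.

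The direction depends on these inputs. With s(ASD) = 0.8, p(ASD) = 0.10, s(BD) = 1.0 and p(BD) = 0.30, starters give 0.72 − 0.70 = +0.02 and stabilised patients 0.8 − 1.0 = −0.20. The selection then works against ASD-BD. With equal s and equal p, both differences are 0.

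**Effect on power.** If total loss by T2 from 25 per group were 30%, 40% or 50% (assumed), 17, 15 or 12 per group would remain, rounding down. One-sided power at 1.06 would be 0.92, 0.88 or 0.81 against 0.95 planned.

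**The case against.** The strongest reply is that this is a condensed article. It defines no analysis set and no handling of discontinuation, and a fuller document may do so. That stands as far as it goes: the article does not say that the analysis is restricted to stabilised patients, and the absence of an analysis set is not the point here. The visit anchor, however, is stated, and it contradicts the sentence before it.

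Several stronger readings are tempting and are not supported.
- A reader might infer that anyone who stops lithium has no follow-up. Patients who stop after stabilising have datable visits. Major adverse events are monitored regardless, and the adverse-event history at T1 can pick up early events in patients who later stabilise. The gap is in scheduled assessments for those who never stabilise.
- A reader might infer that the bias always runs towards similarity. The second example above shows that it need not.
- A reader might infer that the 20% dropout excludes losses before a stable dose. Section 2.5 ties it to six months of follow-up, and Section 2.3 starts follow-up at recruitment, so it can equally be read as including them. The text leaves this open.

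It can also be said that outcome at a stable dose is a legitimate on-treatment question. That is true, and it is a reason to keep it as a secondary analysis. It does not show how lithium performs in all who start it.

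**Conclusion.** The concern holds in this limited form. The contradiction in Section 2.3 is on the face of the text and needs no assumption. So is the consequence that lithium starters who never reach a stable dose have no scheduled efficacy or tolerability assessment after T0.

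Both aims are therefore conditioned on a post-treatment event and may be biased, in a direction not known in advance. If failure to stabilise is commoner in ASD-BD and those patients do worse, the bias favours the non-inferiority hypothesis. The 0.2 SD (0.1 to 0.3) is an illustration from assumed rates, not an estimate for this trial. The length of the timing gap and the loss of power also rest on assumed inputs.

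**What to change.** - Reconcile the Abstract and the two sentences in Section 2.3 to a single time origin.
- Date the three- and six-month outcome assessments from the first lithium dose for everyone who starts, including those who stop or do not stabilise.
- Count side effects and discontinuations from the first dose.
- Report by group the proportion reaching a stable dose and the time taken to reach it.
- Keep results measured from steady state as a secondary analysis.
- State in Section 2.5 whether the 20% dropout includes losses before a stable dose.

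The cost is a short amendment to assessment timing. There are two drawbacks: some patients will have had less than three months at a stable dose at T1, and patients who have stopped lithium must be asked to attend, which takes effort in a routine-care study. The change concerns when outcomes are measured and who is counted; it implies no change to dosing or clinical management.

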### 2.4. Clinical Measures

The following clinical measures will be administered as detailed above:-CGI: this item evaluates the severity of the disease based upon the clinician’s judgement and expertise by coding it on a 7-point scale from 1 = “normal” to 7 = extremely severe”;-CGAS: this item provides a measure of the degree of functional impairment due to the disease, in terms of social, familiar and school functioning, by coding it on a 100-point score, with values greater than 60 indicating significant clinical impairment;-CDRS: this 17-item rating scale assesses the severity of depressive symptomatology on a total score ranging from 17 to 113 based on single items rated from 1 to 5 or 7;-YMRS: this frequently used rating scale aims to assess manic symptoms in youth and is composed of 11 items subjectively rated by the clinicians based on the last 48 h before the interview;-C-SSRS: this tool is a clinical interview that comprehensively assesses suicidal thoughts and behaviors by investigating their presence, severity, and frequency, including specific sections dedicated to the severity of suicidal ideation, its intensity, the frequency of occurrence of suicide attempts, both failed and interrupted, and self-injurious behaviors, and the lethality of completed suicide attempts;-DSHI: this self-reported questionnaire is composed of 17 items exploring the presence of several different types of non-suicidal self-injurious behaviors, by specifying, for each type, their frequency and intensity;-RIPoSt-Y: this self-rated measure evaluates the presence of ED in youth based on 31 items distributed across three different subscales, including Affective Instability, Emotional Reactivity, and Interpersonal Sensitivity, by providing, for each, a clinical cutoff;-MOAS: this interview is administered to parents or caregivers to measure four types of aggression, including verbal aggression, aggression towards objects, and self-directed and others-directed aggression, by providing a 4-level severity score;-ARI: this parent-reported questionnaire evaluates the presence of irritability in the last six months and is composed of six items rated from 0 to 2 and a seventh item related to the degree of functional impairment.

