### 2.2. Recruitment

Patients will be consecutively enrolled after assessment at our hospital for eligibility. Those who meet the eligibility criteria listed below will be included following a thorough clinical screening. All participants and their caregivers will be informed about the assessment procedure, and participation in the study will be voluntary. Recruited patients and their parents will be asked to provide their signed informed consent. Additionally, patients will be allowed to withdraw their consent any time during the study.

Inclusion criteria will be as follows: lithium-naïve adolescent inpatients or outpatients aged 12 to 18 years; informed consent obtained from the patient and both caregivers; diagnosis of Bipolar or Related Disorders (Bipolar Disorder type I (BD-I), Bipolar Disorder type II (BD-II), Cyclothymic Disorder, Other Specified or Unspecified Bipolar Disorder) with or without a diagnosis of Autism Spectrum Disorder according to the Diagnostic and Statistical Manual of Mental Disorders, Fifth Edition, Text Revision (DSM-5-TR); cognitive functioning within the borderline to normal range (i.e., Full-Scale Intelligence Quotient (FSIQ) or General Ability Index (GAI) ≥ 70); current presence of Self-Injurious Thoughts and/or Behaviors (SITB) (i.e., including non-suicidal self-injury (NSSI), intentional self-harm, suicide ideation, plans or preparations, or suicide attempts) as assessed through clinical interview (i.e., investigated by administering the Columbia—Suicide Severity Rating Scale); current presence of Emotional Dysregulation (ED) and/or irritability as assessed by means of standardized clinical measures (i.e., Reactivity, Intensity, Polarity, and Stability questionnaire for Youth and/or Affective Reactivity Index above the clinical cutoff). These latter criteria will be considered to ensure a relatively high clinical severity of the included sample.

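### The six-month ARI look-back given at T1 starts three months before steady state, so the T0-to-T1 ARI change can mix pre-treatment and on-treatment irritability

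*Protocol article*

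**What the plan says.** Section 2.4 describes the ARI thus: "this parent-reported questionnaire evaluates the presence of irritability in the last six months". Section 2.3 has caregivers complete it at every visit. T0 is before lithium starts, and the later visits fall "three (T1) and six (T2) months after reaching stable drug dosage". The article gives no different recall period for the repeat visits and no time from first dose to steady state.

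The scale has two roles. It is one of the two entry measures in Section 2.2 (RIPoSt-Y and/or "Affective Reactivity Index above the clinical cutoff"). It also informs an outcome domain: the Abstract states "Primary outcomes will include mood instability, suicidality, emotional dysregulation, and aggression", and the Introduction pairs irritability with emotional dysregulation as a focus of the study. Section 2.6 tests score changes on all the listed scales and regresses change on ASD diagnosis, with age, gender, other psychotropic drugs and lithium level as covariates. It makes no exception for the ARI at T1.

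**The concern.** A change score is interpretable as on-treatment change only if the follow-up score describes time on treatment. A six-month question asked three months after steady state also asks about titration and, if titration is short, about untreated months that the T0 rating already covered. The YMRS, by contrast, is described in Section 2.4 as covering 48 hours, so T1 scores on the two scales describe very different periods.

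At stake is the T0-to-T1 ARI change, both within groups and as an outcome in the regression on ASD diagnosis. The untreated share of the window depends on each patient's titration time, which is not among the covariates in Section 2.6.

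**Working it through.** The plan gives no figure of its own on this point, so the check is calendar arithmetic.

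**Inputs**
- Recall window: 6 months (Section 2.4).
- T1 and T2: 3 and 6 months after steady state (Section 2.3).
- k, months from first dose to steady state: not stated, so a range is assumed.

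**Step 1: time before steady state.** At T1 this is 6 − 3 = 3 months, or 3/6 = 50% of the window, whatever k is. At T2 it is 6 − 6 = 0.

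**Step 2: time before the first dose.** Share at T1 = max(0, 6 − 3 − k)/6. Share at T2 = max(0, 6 − 6 − k)/6, which is 0 for every k.

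| k (assumed) | Pre-lithium months in T1 window | Share at T1 | Share at T2 |
|---|---|---|---|
| 0 | 3 | 50% | 0% |
| 0.5 | 2.5 | 42% | 0% |
| 1 | 2 | 33% | 0% |
| 2 | 1 | 17% | 0% |
| 3 or more | 0 | 0% | 0% |

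**Step 3: effect on the measured change.** Suppose caregivers average evenly over the window, irritability was level before treatment, and the full effect is present from the first dose. The T0-to-T1 change is then multiplied by 1 − share: 0.50, 0.58, 0.67 or 0.83 for k = 0, 0.5, 1 or 2. If the effect is absent until steady state, the multiplier is 3/6 = 0.50 for any k. If caregivers weight recent weeks more heavily, it moves towards 1.

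**Step 4: effect on the group comparison,** under the first set of assumptions in Step 3.
- Same k in both groups, say 1 month: a true difference in change is multiplied by 0.67, so it shrinks.
- Different k, same true change D: with k = 0.5 in one group and 2 in the other, the measured changes are 0.58D and 0.83D. This is an apparent difference of 0.25D where none exists.
- Different k, different true change: if the k = 2 group truly changes by only 0.70 of the other group's change, it shows 0.70 × 0.83 = 0.58, and the k = 0.5 group shows 1 × 0.58 = 0.58. A real difference disappears.

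**Step 5: the other visit clock.** Section 2.3 also says "Both groups will be followed up for six months after recruitment while receiving treatment with Extended-Release Lithium Salts", and the Abstract gives plain three- and six-month visits. If T1 fell three months after recruitment, at least half of its window would be before lithium. The T2 window would then begin at recruitment and could include any gap before the first dose. The mismatch at T1 is present on either clock; the clean T2 window depends on counting from steady state.

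**The case against.** The best case against the point is that it is small and conditional. The ARI is one of nine scales in Section 2.4. The Abstract's primary list names emotional dysregulation, which Section 2.4 assigns to the RIPoSt-Y without a six-month window. The sample size rests on the YMRS and is untouched. The six-month contrast is clean on the steady-state clock. An instruction to rate only the time since the last visit could also sit in the full protocol. All of this limits the weight of the point. The last argument is weak, because the article states six months without qualification.

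Four stronger readings are tempting, and the documents do not support them.
- **That the flaw favours non-inferiority.** This follows only if dilution is equal in both groups. Step 4 shows that unequal titration can create, hide or enlarge a difference.
- **That titration must be close to zero,** because follow-up is limited to six months after recruitment while T2 is six months after steady state. Those statements conflict, and the conflict is not evidence of how long titration takes.
- **That power at T1 can be worked out** by shrinking the effect size of 1.06. That figure was chosen for the YMRS, and nothing in the article carries it over to the ARI.
- **That the three-month overlap of the T1 and T2 windows adds bias.** It has no bearing on changes from T0. It would matter only for a T1-to-T2 contrast, which Section 2.6 does not name specifically.

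**Conclusion.** The point holds as a limited one. It is certain from the article's own text that half of the T1 ARI window precedes steady state. It is conditional that part of it precedes the first dose: this needs titration of under three months, and the 42%, 33% and 17% shares are illustrations for assumed times. That the T1 change is understated rests on two further assumptions: caregivers rate the whole window, and irritability falls on treatment. The amount of shrinkage also depends on how they weight the months and how quickly the effect appears. The direction of any error in the ASD versus non-ASD comparison cannot be fixed without knowing titration time by group.

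The consequence is confined to one scale at one interim visit. It is still worth correcting, because the plan as written would analyse that change as if it were on-treatment change in a domain on which the study focuses.

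**What to change.** State in Section 2.6 that ARI inference, within groups and in the regression on ASD diagnosis, uses the T0-to-T2 change, and that T1 ARI scores are reported descriptively with the recall window noted. This takes about one line, leaves the sample size unchanged and does not touch treatment. The cost is that there is no inferential ARI result at T1. The two visit clocks in Section 2.3 should be reconciled at the same time, since the clean T2 window relies on counting from steady state.

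A secondary alternative is one shorter recall window, the same at T0, T1 and T2 and no longer than the three months since steady state, with the six-month form kept at T0 for eligibility only. This preserves T1 inference, but it departs from the window the article describes and adds a second ARI form at baseline.
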